#### Negative Effects and Adverse Events

(Serious) adverse events ((S)AEs) will be monitored and assessed in different ways through online questionnaires and structured interviews, adapted from the recommendations of the National Institute for Health Research (57) as well as from Horigian and colleagues (58).

(S)AEs can be reported to the E-Coaches during the intervention or to the study team via email or during the structured clinical interviews.

The deterioration rate will be one measure of possible negative effects of the iCHIMPS intervention. Deterioration is defined as worsening in the assessed mental health of the participant using the Reliable Change Index [RCI; (59, 60)].

Additionally, negative effects of psychological treatments experienced by the participant will be measured during the online assessments by the Negative Effects Questionnaire [NEQ; (61)]. The scale consists of 20 items and is divided into five subscales, namely symptoms, quality of treatment, dependency on the treatment, stigma, and hopelessness. The subscales are ranging in their internal consistency from Cronbach's α 0.72–0.93, while the whole scale shows a Cronbach's α of 0.94 (61, 62).

During the online self-report questionnaires (YSR; items 18 and 93) and during the structured clinical interviews (Kiddie-SADS-PL; depression chapter section 4 and 5) suicidal and self-injurious tendencies and behaviors will be assessed.

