**Figure 1 F1:**
[figure not shown]
Flow chart.

If the potential family meets the inclusion criteria for families and all necessary parties have signed the informed consent as well as the contact forms, a clinical assessment interview will take place, either at the clinics or via phone. The inclusion and exclusion criteria will be written down and transferred to the study team at Ulm University together with the other forms. This marks the end of the recruitment procedure at the adult mental health clinics.

After the recruitment at the clinics is finalized and the inclusion criteria are fulfilled, the participants and possibly their parents and/or legal guardian(s) will receive a personalized link for the online assessment. After the successful completion of the online baseline assessment (t0) by at least the participant and the parent with the mental disorder, the family is eligible to be included into the trial and will be randomized according to the randomization list by a scientist at Ulm University.

Depending on the group the family was randomized to, an email will contain the explanation of the procedure of the internet-based intervention and the following online assessments (iCHIMPS) or the explanation of why they will not receive access to the internet-based intervention and the procedure of the following online assessments (TAU).

If the participant was assigned to iCHIMPS, he or she is able to log into the internet-based intervention at https://patient.esano-trainings.de and complete the eight consecutive modules of the internet-based intervention at her or his own pace.

All participants (ICHIMPS and TAU) and possibly their parent(s) and/or legal guardian(s) will receive emails with an invitation to the online assessments for t1 (one-month post-inclusion), for t2 (two-months post-inclusion) and for t3 (six-months post-inclusion).

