The main topics of the intervention are the engagement with the users own life situation, their own challenges, resources and strengths as well as the engagement about the mental disorder of their parent(s). Further covered topics include health, communicating about difficult topics, strengthening familial and social relationships, stress management, emotion regulation and establishing healthy boundaries to increase autonomy (an overview of the modules is provided in Table 1). The techniques used are based on cognitive behavioral therapy, such as cognitive restructuring, on mindfulness-based therapy as well as psychodynamic therapy, such as clarifying their own life situation and careful reflection about dysfunctional communication or relationship patterns.

**Table 1 T1:** Overview of intervention modules.

**Modules**		**Content**
1	What can you expect?	Introducing the team, literature and guiding principles; Familiarising with the iCHIMPS process, overview of the modules and E-Coaching
2	The first step – get to know yourself and your challenges.	Strengths and worries of the participants; Identifying one's values, goals and resources; Challenges in everyday life with a mentally ill parent
3	Knowledge means strength – find out more about your parent's mental illness.	Psychoeducation; Family coping with illness
4	Talk about it – stay in contact and learn to talk about difficult subjects.	Relevance of communication, rules for successful communication, talking about your parent's mental illness with different groups of people
5	Find inner peace – learn how to cope with stress.	Stress management; Possibilities for coping with stress
6	The world of emotions.	Explaining Emotions; Coping with negative Feelings, promoting pleasant feelings
7	You, yourself and your rough edges – learn how to set limits.	Setting limits; Strengthen your self-esteem
8	Last stop! – What is next?	Summary of Modules 2–7; Recognition of warning signs and prevention

Additionally, the internet-based intervention can be complemented by a varying amount of human support. E-Coaches can provide guidance through individualized feedback on each section and answer potential questions in an asynchronous fashion. E-Coaches in the present study are children and adolescents' psychotherapists (in training) who undergo a specialized workshop and regular supervision.

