#### Economic Outcomes

Health related life quality of the participant assessed by the self-report questionnaire EuroQol-5-Dimensions-Youth [EQ-5D-Y; (49–52)]. The questionnaire consists of two parts. In the first part the participant defines his or her actual health state on the five dimensions mobility, self-care, usual activities, pain/discomfort and anxiety/depression. Each dimension is rated between 1 representing the best health state and 3 representing the worst health state. The overall health state is a 5-digit number representing the rating values for each health state. For the generation of QALYs, the overall health states will be valued using utility value sets generated by means of discrete choice experiments with representative samples from the general population (53, 54). In the absence of a national value set the visual analogue scale provided in the second part of the EQ-5D-Y can be used to value the overall health state.

Utilization of the health care system by the participant as measured by the self-report Children and Adolescent Mental Health Services Receipt Inventory (55, 56). This questionnaire assesses utilization of in- and outpatient health care as well as psychosocial care provided by the child welfare services and school based support provided by the educational system (56).

Health insurance claims data provided by one of the participating German health insurance companies, BARMER, DAK, KKH, TK, MKK, IKK Classic, AOK Baden-Württemberg or AOK Hessen, include information about the utilization of the health care system by members of the participating family who are insured by one of the aforementioned health insurance companies. The claims data consists of all treatment services provided by inpatient and outpatient care, medication, remedies, rehabilitation, and sick leave. All available information can be merged via an pseudonymized identification number for each patient. For every treatment service, all costs from health insurance perspective are documented for the period from January 1^st^ 2018 to June 30^th^ 2022.

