#### Safety Procedure of (S)AEs

The occurrence of (S)AEs within the diagnostic interviews during the recruitment phase will be handled by the medical health professionals at each clinic, who also decide whether a study participation based on the inclusion and exclusion criteria is possible. Similarly, the occurrence of (S)AEs during the diagnostic interviews at t3, conducted by the study team at the University Medical Center Hamburg-Eppendorf, will be handled by medical health professionals of the local study team.

The occurrence of (S)AEs during the online assessment as well as during the internet-based intervention follows a step wise protocol and clear documentation rules and is handled by the study personnel at Ulm University. In case of (S)AEs, the participant will automatically receive an email with information on help as well as emergency numbers. The study personnel will contact participants who gave critical answers directly. If the participants are not reachable within 48 h on weekday the responsible authorities will be informed.

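### E-Coaches are an (S)AE reporting route in the iCHIMPS arm only, so by-arm totals of all reported events would be tilted against iCHIMPS by unequal detection

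*Protocol article*

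**What the plan says.** The section on negative effects and adverse events opens by saying that (S)AEs "will be monitored and assessed in different ways through online questionnaires and structured interviews". It then names the reporting routes: "S)AEs can be reported to the E-Coaches during the intervention or to the study team via email or during the structured clinical interviews". The same section adds a deterioration rate based on the Reliable Change Index, the NEQ, YSR items 18 and 93, and the suicidality parts of the Kiddie-SADS-PL.

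The Intervention section describes the coaching: "E-Coaches can provide guidance through individualized feedback on each section and answer potential questions in an asynchronous fashion". It says the amount of human support can vary. The Discussion nevertheless calls the intervention guided, and working alliance with the E-Coach is a planned covariate.

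Under Procedure, families randomised to the control arm receive an e-mail with "the explanation of why they will not receive access to the internet-based intervention and the procedure of the following online assessments (TAU"). In both arms participants "will receive emails with an invitation to the online assessments for t1 (one-month post-inclusion"), and likewise for t2 and t3.

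The safety procedure treats events from the intervention together with those from the questionnaires: "The occurrence of (S)AEs during the online assessment as well as during the internet-based intervention follows a step wise protocol and clear documentation rules". The Introduction includes potential adverse events in the fifth trial objective. The Statistical Analysis section makes only the YSR total score at t3 confirmatory and describes no (S)AE test.

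**The concern.** A count of adverse events depends on how many events occur and on how hard one looks. Here one arm has an additional observer. E-Coaches, who are psychotherapists or in training as such, may give individual feedback across up to eight modules and can receive event reports while doing so. Nobody has that role for TAU adolescents.

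A two-arm trial that names adverse events in an objective and reports under CONSORT will naturally show (S)AEs by arm. If those totals mix all routes, an excess in iCHIMPS may reflect better detection rather than harm. Equally, a real excess could be explained away as detection. Nothing in the article limits a comparison to shared sources or separates reports by route.

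**Working it through.** The plan gives no (S)AE rate, detection rate or (S)AE test, so there is no stated figure to reproduce. The check first sets out the sources by arm and then illustrates the effect with assumed values.

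**Sources after baseline, by arm**

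| Source | iCHIMPS | TAU |
|---|---|---|
| Online questionnaires at t1, t2, t3 (YSR, including items 18 and 93) | yes | yes |
| Deterioration (RCI), if computed on the YSR | yes | yes |
| Kiddie-SADS-PL at follow-up | if held | if held |
| Unsolicited e-mail to the study team | yes | yes |
| E-Coach or platform during the modules | yes | no |

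Two entries need a note.
- **Interviews:** Table 2 marks the Kiddie-SADS-PL at t0 only, Completion Times places it at t0, t2 and t3, and the safety procedure speaks of interviews at t3.
- **RCI:** the text ties the index to assessed mental health without naming the instrument. The YSR is the self-report measure taken at t0 to t3.

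**Illustration (assumed values)**

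Let the true (S)AE risk r be equal in both arms. The shared sources detect a proportion p of events. E-Coaches independently detect a proportion q, in iCHIMPS only.

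- Recorded risk in TAU: r × p
- Recorded risk in iCHIMPS: r × [1 − (1 − p)(1 − q)]
- Apparent risk ratio: 1 + q(1 − p)/p, whatever the value of r

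| p | q = 0.1 | q = 0.3 | q = 0.5 |
|---|---|---|---|
| 0.4 | 1.15 | 1.45 | 1.75 |
| 0.6 | 1.07 | 1.20 | 1.33 |
| 0.8 | 1.03 | 1.08 | 1.13 |
| 1.0 | 1.00 | 1.00 | 1.00 |

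Worked case at the unfavourable corner, with r = 0.20, p = 0.4 and q = 0.5:
- TAU records 0.20 × 0.4 = 8%.
- iCHIMPS records 0.20 × (1 − 0.6 × 0.5) = 14%.
- With the planned 153 participants per arm, a two-sided 5% level and clustering ignored, a simple comparison of proportions would declare a false excess in iCHIMPS about 39% of the time.

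With r = 0.10 and the same p and q, the figures are 4% against 7%, and about 21%. With p = 0.8 the chance is between about 3% and 7% for r of 0.10 or 0.20 and q from 0.1 to 0.5.

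**After the fix:** if only sources scheduled alike in both arms enter the comparison, q drops out and the ratio under equal true risk is 1.00, provided completion is equal in both arms.

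**The case against.** The strongest reply is that the article contains no biased comparison. It states no between-arm (S)AE test, and the sentence about E-Coaches describes routes for spontaneous reports. Systematic assessment is said to run through questionnaires and interviews, which both arms receive. The stepwise protocol and its documentation rules are not shown and may already record where each report came from. How safety tables are built is commonly left to the full protocol or SAP.

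Much of this stands. The point is conditional on pooled counts being compared by arm, and it cannot be said that the event source goes unrecorded. What remains is that the article itself sets out the unequal routes, puts adverse events into an objective and names no offsetting rule. If the source is not captured when an event is recorded, no later analysis plan can separate the routes.

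A reader might go further in three ways that the document does not support.
- **All safety results are uninterpretable.** They are not: RCI deterioration and YSR items 18 and 93 come from assessments scheduled alike in both arms.
- **TAU has three detection points and iCHIMPS eleven (3 + 8).** Modules are self-paced, coaching is asynchronous and variable in amount, and no text says E-Coaches screen for events. That count also leaves out any follow-up interviews. The gap in scheduled assessments between months 2 and 6 applies to both arms.
- **Failing to use CAMSHRI-DE inpatient care for safety is an error.** The plan assigns that instrument to the economic evaluation, which is a legitimate choice.

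**Conclusion.** The asymmetry is in the text, and its direction is clear: pooled (S)AE counts by arm would be tilted against iCHIMPS. The size is unknown. The ratios of about 1.03 to 1.75 rest on assumed shared detection of 40% to 80%, added E-Coach detection of 10% to 50%, independence of the two, equal true risk and equal questionnaire completion. The bias vanishes if the shared sources miss nothing or coaching adds nothing.

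The point concerns the collection scheme and any by-arm table of pooled (S)AEs under the fifth objective. It does not concern a stated test, the confirmatory YSR analysis, or the safety measures already scheduled alike in both arms.

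**What to change.** Add to the section on negative effects and adverse events that the between-arm safety comparison rests on sources scheduled identically in both arms:
- YSR items 18 and 93 at t1 to t3;
- RCI deterioration, naming the YSR as its instrument;
- the Kiddie-SADS-PL suicidality sections at follow-up, once Table 2, Completion Times and the safety procedure are reconciled on when those interviews take place.

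CAMSHRI-DE inpatient care at t3 could be added but is optional.

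Record the source of every (S)AE. Continue to report all events, with those known only through E-Coaches or the platform listed separately for iCHIMPS.

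The cost is a sentence or two of text and one source field on the event form, if the documentation rules do not already have it. No new participant data are needed and the handling of events is unchanged. The drawback is fewer events in the comparative table, and unequal questionnaire completion could still affect it.

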#### Completion Times

The Kiddie-SADS-PL interview will take 45 to 75 min to administer and will be carried out at t0 with the participant and the parent(s) as well as at t2 and t3 with the participant.

The M.I.N.I. interview takes ~15 min to administer and will be carried out with the parents with a mental disorder at t0.

Online self-report questionnaires for the participants will take ~60 min at t0, t2 and t3 as well as ~30 min at t1.

Online self-report questionnaires for the participating parents will take ~20 min at t0, t1, t2 and t3.

#### Reimbursement

Only the participating adolescents will be compensated for their participation after the successful completion of the online assessment at t2 and t3 with each 20 €. Reimbursement will be transferred to a bank account of their choice.

#### Data Management, Quality Assurance, and Safety Measures

All interviews will be conducted in person or via phone at the recruiting clinics and at the University Medical Center Hamburg-Eppendorf. The collected pseudonymized datasheets will be stored at the clinics until the end of each quarter and then sent to the study team of Ulm University. At Ulm University, the data will be stored and later transferred to the study team of the University Medical Center Hamburg-Eppendorf to be entered into the data management system provided by the data management company CTC North.

Online assessments will be carried out via the survey platform Lime Survey. The platform is based on servers located at Ulm University. All collected data will be stored pseudonymized. Data from the online assessments will be transferred to CTC North at the end of each quarter.

The CTC North will receive a list of all participants and/or their parents who are insured at one of the participating health insurance companies. Each cooperating health insurance company will then send the health insurance claims data from each participating family member who is a member of their insurance to CTC North.

At CTC North the data from all different sites will be collected and combined. Afterwards the evaluating partners will receive pseudonymized data sets for their respective analyses.

CTC North is additionally responsible for the monitoring of the data management measures at each recruiting clinic.

#### Safety Procedure of (S)AEs

The occurrence of (S)AEs within the diagnostic interviews during the recruitment phase will be handled by the medical health professionals at each clinic, who also decide whether a study participation based on the inclusion and exclusion criteria is possible. Similarly, the occurrence of (S)AEs during the diagnostic interviews at t3, conducted by the study team at the University Medical Center Hamburg-Eppendorf, will be handled by medical health professionals of the local study team.

The occurrence of (S)AEs during the online assessment as well as during the internet-based intervention follows a step wise protocol and clear documentation rules and is handled by the study personnel at Ulm University. In case of (S)AEs, the participant will automatically receive an email with information on help as well as emergency numbers. The study personnel will contact participants who gave critical answers directly. If the participants are not reachable within 48 h on weekday the responsible authorities will be informed.

### Statistical Analysis

#### Clinical Analyses

All statistical analyses will be conducted according to the intention-to-treat principle (ITT). The ITT population includes all study participants of all families that have been randomized. Type 1 error rate (two-sided hypothesis) will be set to 5%. Depending on the level of measurement of each variable descriptive statistics will be reported either for the whole sample or separated by groups.

Due to the fact that family members are subject to common influences, cluster effects are to be expected. Inferential statistics will therefore be conducted with a mixed-models approach (family and participant as random effects). Recruitment site, group membership, time point, and baseline value of each outcome as well as interaction between group membership and time point, as appropriate, will be added as covariates to the model. Endpoints will be operationalized as change from baseline value. Missing values will be direct imputed within the mixed model approach to enable an ITT analysis.

The result of the primary analysis is the between group contrast of the YSR total problems score at t3 (6-months post-inclusion) within the ITT population. Only this comparison will be considered as confirmatory. Additionally, the analysis will be repeated with the per-protocol (PP) population. Secondary endpoints will be evaluated on an exploratory basis with similar models.

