#### Sample Size and Power Calculations

The sample size calculation was conducted with the Power Analysis and Sample Size Software (PASS 15) and is approximated based on the “Tests for Two Means in a Cluster-Randomized Design” module. As clinically significant mental health effect a moderate effect size of 0.5 (Cohens *d*) in the primary outcome (Youth Self Report score; YSR 11-18R; 32) between the two groups (iCHIMPS vs. TAU) at 6-months post inclusion has been assumed. Calculating with a power of 80%, a significance level of 0.5% (two-sided hypothesis), an inter-cluster correlation coefficient of 5%, and a family size of 1.3 children between the age of 12 years and 0 months and 18 years and 11 months per family, 65 participants in 50 families per group (130 participants in 100 families in total) are needed. Considering a drop-out rate for online-interventions of 50–60%, our trial will aim at 306 participants in 234 families (153 participants in 117 families per group) as has been estimated in the original grant application.

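### Fitted as written, the primary mixed model implies equal variance and correlation at 1, 2 and 6 months, so the standard error of the confirmatory 6-month contrast is too small if correlation with baseline fades over time

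*Protocol article*

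**What the plan says.** Under Statistical Analysis, Clinical Analyses, the protocol article states: "Inferential statistics will therefore be conducted with a mixed-models approach (family and participant as random effects"). Recruitment site, group, time point and the baseline value of each outcome are fixed terms, "as well as interaction between group membership and time point, as appropriate, will be added as covariates to the model". Endpoints are changes from baseline, and missing values are to be handled inside the mixed model.

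The confirmatory result is fixed: "The result of the primary analysis is the between group contrast of the YSR total problems score at t3", in the intention-to-treat population. On the level, the section says "Type 1 error rate (two-sided hypothesis) will be set to 5"%.

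The Procedure section and the assessment table place the Youth Self Report (YSR) at baseline, 1, 2 and 6 months. The sample size section plans for 50–60% drop-out. No random slope, visit-specific variance, residual matrix or robust standard error is mentioned, and no SD by visit or between-visit correlation is given.

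**The concern.** A participant intercept and a family intercept with independent, equal-variance residuals give every follow-up visit the same variance and every pair of visits the same correlation. Two features of this trial make that doubtful. The visits are unevenly spaced, with a four-month gap before t3. The outcome is change adjusted for baseline, whose residual variance grows as the correlation with baseline falls. If t3 is the most variable visit, its standard error is pooled with the quieter t1 and t2 and comes out too small.

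At stake is the false-positive rate of the one confirmatory comparison. The same covariance also determines how t1 and t2 inform the missing t3 values.

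A second matter is separate. A contrast at t3 exists only if group-by-time is in the model, and the sentence adding that term qualifies it. Without it, the model estimates an average effect over visits.

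**Working it through.** **1. The plan's own figure.** Inputs from Sample Size and Power Calculations: "a moderate effect size of 0.5 (Cohens *d*) in the primary outcome", "Calculating with a power of 80"%, "an inter-cluster correlation coefficient of 5"%, and 1.3 children per family. The printed level is "a significance level of 0.5% (two-sided hypothesis"), against 5% in Clinical Analyses.

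- Design effect: 1 + (1.3 − 1) × 0.05 = 1.015.
- Level 5%: n = 2(1.960 + 0.842)²/0.5² = 62.8 per group; × 1.015 = 63.7; ÷ 1.3 = 49.03, so 50 families and 65 participants. This matches the article.
- Level 0.5%: n = 106.5; × 1.015 = 108.1; ÷ 1.3 = 83.2, so 84 families and about 109 participants. This does not match.
- Target: 130/(1 − 0.575) = 306, within the planned drop-out range.

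The size calculation therefore used 5%, and 5% is the benchmark below. The printed 0.5% is a separate inconsistency.

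**2. Mechanism.** With unit SDs, the residual variance at visit j after adjusting for baseline is about 1 − ρⱼ², where ρⱼ is the correlation with baseline. Let r be the t3 residual variance divided by the mean over the three visits. With complete data, the actual size of a nominal 5% test using the pooled variance is 2[1 − Φ(1.96/√r)]. This gives 5.0% at r = 1.0, 7.4% at 1.2, 8.6% at 1.3 and 11.0% at 1.5. A size of 8–12% needs r of about 1.25 to 1.59.

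The correlations below are assumptions:

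| Assumed ρ at t1/t2/t3 | 1 − ρ² at t1, t2, t3 | Mean | r | Size by formula |
|---|---|---|---|---|
| 0.65/0.65/0.65 (compound symmetry) | 0.578, 0.578, 0.578 | 0.578 | 1.00 | 5.0% |
| 0.72/0.69/0.62 (mild decay) | 0.482, 0.524, 0.616 | 0.540 | 1.14 | 6.6% |
| 0.75/0.70/0.58 (moderate decay) | 0.438, 0.510, 0.664 | 0.537 | 1.24 | 7.8% |
| 0.78/0.68/0.49 (stronger decay) | 0.392, 0.538, 0.760 | 0.563 | 1.35 | 9.2% |

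**3. Simulation.** Each scenario used 1,500–2,000 trials with no true effect: 234 families, about 1.3 children each, ICC 0.05. The model was fitted by REML with family and participant intercepts, independent residuals, change from baseline, baseline and group-by-time. Site was not modelled. Monte Carlo error near 5% is √(0.05 × 0.95/1500) = 0.6 percentage points.

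| Scenario | Size at t3, no drop-out | Size at t3, 55% drop-out by t3 |
|---|---|---|
| Compound symmetry | 5.2% | 4.7% |
| Mild decay, SD falling to 0.9 at t3 | 4.9% | 5.7% |
| Mild decay | 7.4% | 7.2% |
| Moderate decay | 8.1% | 8.9% |
| Stronger decay | 9.2% | 11.5% |
| AR(1), 0.9 per month | 12.1% | 16.7% |

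The most extreme cases reached about 20%.

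**4. Remedies.** A family-clustered sandwich standard error on the same model gave 4.3–6.2% in all scenarios. An ANCOVA at t3 alone with family-robust errors, run in six scenarios, gave 4.6–6.3%. An unstructured covariance gave 4.1–5.1% in a separate simulation of 600–900 trials per scenario that omitted family clustering; it was not refitted with clustering.

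**5. Interaction left out.** With no effect at any visit, size stayed at 4.6–5.4%. With a true effect of 0.3 SD at t1 and t2 and none at t3, that model rejected in 79–86% of trials, because it no longer tests t3.

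**The case against.** The strongest reply is that the article never says the residuals are independent or homoscedastic. Random intercepts can be combined with a structured residual matrix or robust errors, and such detail usually sits in an analysis plan, which is not shown. This stands against a reading that a reader might infer, namely that the plan forces equal variance; it does not. What remains is that the article states a dependence structure, and its ordinary reading is a poor fit for these visits.

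A reader might also take 8–12% as the trial's actual error rate. The documents do not support that: they contain no visit SDs or correlations, and compound symmetry or a falling SD at t3 leaves the size near 5%.

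Nor does heavy drop-out always make matters worse. It hardly changed the error under mild or moderate decay, and clearly raised it only under stronger decay or AR(1).

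Finally, a reader might infer that the qualified interaction adds to the inflation, or that the plan intends to drop it. Under a global null its omission leaves the size near 5%, and the stated t3 contrast already implies the term for the YSR. The qualifier may be meant for outcomes with fewer visits. This part is a clarification.

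**Conclusion.** The point holds conditionally. If the two random effects are intercepts and the residuals are ordinary, and if residual variance at t3 exceeds that at t1 and t2, the model-based standard error of the confirmatory contrast is too small. The reference range is about 5% to about 12% type I error, with higher values only in extreme scenarios. All of these figures depend on assumed correlations. The interaction wording is a separate and smaller matter that affects what is estimated. Overall this is a cheap improvement worth making before analysis; it does not show that the trial's test is invalid.

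**What to change.** For the primary YSR model, keep the family random intercept and replace the participant random intercept with an unstructured within-participant covariance over t1–t3, reading the group contrast at t3. Family-clustered robust standard errors on the stated model are an acceptable alternative for the size of the test. The unstructured form has the added merit that the missing-data handling relies on the same covariance.

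As a separate sentence, state that group-by-time is always included for the primary outcome, and confine the qualifier to outcomes with fewer visits. Baseline-by-time and Kenward-Roger degrees of freedom are optional refinements.

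Cost: wording only. Three visits need six covariance parameters instead of two, so four more, with no extra participants or assessments. The standard error will be slightly larger where the simpler model was over-optimistic.
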